### Randomization and blinding

Eligible and consenting participants are randomly assigned to the FSN group (n = 30) or the drug group (n = 30) for the clinical study at a 1:1 ratio through a central randomization system. The randomization sequences are generated by staff using the SAS program. Patient serial numbers, random numbers, and grouping results are assembled into random assignment cards that are then sealed in disposable opaque envelopes. The cards in the envelopes have serial numbers that match the numbers on the envelopes. The random assignment cards are kept in a special place. When eligible participants enter the study, envelopes with the same serial numbers are opened in the order of the participants. Participants are grouped and treated according to the cards they obtain.

Due to the specific nature of the needling operation, the participants and practitioners involved in this study are not blinded. However, outcome assessors are blinded to the group assignments and instructed not to communicate with participants regarding the intervention to ensure objectivity in outcome evaluations. The researchers who are responsible for data collection and statistical analyses are also blinded to the assigned tasks to minimize bias in the reporting of subjective results.

### Interventions

Participants’ gender, age, marital and childbearing history, family history, allergy history, smoking and drinking history, past medical history, drug history, and other general information are collected before the formal intervention. The participants’ baseline data, such as weight and BMI, are observed. Visual analogue scale (VAS) measurements, Western Ontario and McMaster Universities (WOMAC) index measurements, joint active range of motion tests, three-dimensional gait analyses, and shear wave elastic imaging technology analyses are performed to comprehensively evaluate the pain level, knee joint movement status and system function, as well as the lower limb skeletal muscle elastic modulus. To ensure participants adhere to protocol requirements for timely FSN attendance or scheduled dosing of celecoxib, education is provided and schedules are distributed. Participants are also instructed to avoid other KOA treatment that may affect efficacy evaluation, such as oral or topical analgesics, manual acupuncture and massage.

### FSN therapy

Operation of the FSN follows the KOA’s Fu’s Subcutaneous Needling Treatment Code of Practice [27]. Participants first assume the supine position. After routine disinfection, a disposable Fu’s subcutaneous needle (Nanjing Paifu Medical Technology Co., Ltd., Jiangsu, China, Fig. 2) is inserted parallel into the subcutaneous loose connective tissue around the pathological tight muscles (gastrocnemius muscle, tibialis anterior muscle, and quadriceps femoris muscle). The protruding part of the hose holder is fixed to the card slot after the needle is completely inserted. Confirming that the participants have no pain, the index and ring fingers alternate back and forth in a smooth, soft, fan-like swaying movement. The fan angle is approximately 60°, and a total of 45 round trips are performed in 30 s. Swaying Movement is accompanied by Reperfusion Approach: 20 sways along with 10 s of Reperfusion Approach are performed as a set of procedures. For each target pathological tight muscle, 2–3 sets of the above procedures are required. The Reperfusion Approach for different pathological tight muscles are as follows: (1) for the gastrocnemius muscle, the participant is placed in the prone position, with the foot extended out of the bed. A towel is placed on the soles of the feet, and the participant is instructed to resist resistance by plantar flexion of the ankle joint; (2) for the tibialis anterior muscle,the participant is placed in the supine position, and the ankle is dorsiflexed to resist counterdirectional forces from the instructor, (3) for the quadriceps muscle,the participant is placed in the supine position. With a foam shaft or other support made of soft material placed in the popliteal fossa, the knee joint is then forcefully extended against resistance from the instructor. The FSN group is treated 3 times a week for 2 weeks. Prior each FSN treatment day, participants are contacted by telephone in advance to schedule specific sessions and are reminded to attend. (Fig. 3).

**Fig. 2 Fig2:**
[figure not shown]
A disposable FSN needle consists of a cannula and a needle core. The practitioner holds the needle handle and manipulates it in a fan-shaped pattern at an angle of approximately 60°

**Fig. 3 Fig3:**
[figure not shown]
FSN entry point and Reperfusion manoeuvre. **A** Quadriceps muscle entry point: 1/3 below the line between the anterior superior iliac spine and the medial superior border of the patella; **B** Quadriceps muscle Reperfusion manoeuvre; **C** Tibialis anterior muscle entry point: 1/3 above the line between the caput fibulae point and the first metatarsal bone; **D** Tibialis anterior muscle Reperfusion manoeuvre; **E** Gastrocnemius muscle entry point: 1/3 below the line between the medial ankle and midpoint of the popliteal fossa; **F** Gastrocnemius muscle Reperfusion manoeuvre. *Notes*: The red arrow shows the participant’s direction of force and the blue arrow shows the instructor’s direction of force

### Oral celecoxib

Participants in the drug group receive 200 mg of oral celecoxib (a capsule) daily for 2 weeks. They are required to mark prepared schedules after each dose. After the seventh and fourteenth doses, participants return to the research center with their schedules for review. They are closely followed up during the administration of the drug, and the treatment will be discontinued immediately in case of adverse events. If necessary, appropriate symptomatic treatments, such as acid suppressing, protection of the gastric mucosa, anti-vertigo medication, etc., will be administered until the adverse events subside.

### Outcomes

The evaluators detect the outcomes at baseline, on day 7, day 14, and during the follow-up period (day 28 and day 42 after the start of the treatment) (Table 1).

**Table 1 Tab1:** Study schedule

Period	Admission day	Baseline assessment	Evaluation on Day 7	Evaluation on Day 14	Follow-up period
Time point	− T1	T0	T1	T2	T3
Enrolment					
Eligibility	⭕				
Informed consent	⭕				
Allocation	⭕				
Interventions					
FSN			⭕	⭕	
Celecoxib			⭕	⭕	
Evaluation					
VAS score		⭕	⭕	⭕	⭕
WOMAC score		⭕	⭕	⭕	⭕
ROM		⭕	⭕	⭕	
3D gait analysis		⭕	⭕	⭕	
Shear wave elastic imaging					
Technology analysis		⭕	⭕	⭕	
Adverse events			⭕	⭕	⭕

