#### Primary outcome

KOA is characterized by knee pain as its predominant symptom. Visual Analog Scale (VAS) scores, ranging from 0 to 100 mm, are utilized to objectively quantify pain levels. The primary outcome of this study is the difference in VAS scores between day 14 and baseline measurements. Participants are instructed to indicate the severity of their knee pain by marking a point on a continuous horizontal line segment, with 0 mm representing minimal pain and 100 mm indicating the most severe pain [28].

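### Table 1 schedules allocation before the baseline assessment, so the self-rated baseline VAS in the primary change score may be marked by participants who probably already know their group

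*Protocol article*

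**What the plan says.** The sentence that introduces Table 1 reads "The evaluators detect the outcomes at baseline, on day 7, day 14, and during the follow-up period". It does not mention allocation; the order comes from the table. The first two columns are headed "Admission day Baseline assessment" and carry the time points −T1 and T0. Eligibility, informed consent and allocation are marked only at −T1. VAS, WOMAC, range of motion, gait and elastography are first marked at T0.

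Randomization and blinding describes how the group becomes known: "When eligible participants enter the study, envelopes with the same serial numbers are opened in the order of the participants", and then "Participants are grouped and treated according to the cards they obtain". The same section states that "the participants and practitioners involved in this study are not blinded". Outcome assessors are blinded.

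The Primary outcome section says: "The primary outcome of this study is the difference in VAS scores between day 14 and baseline measurements". The participant marks the VAS line personally. The Statistical analysis section compares the arms on change from baseline with a t test or a Mann–Whitney U test.

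**The concern.** A baseline value should be fixed before anything that depends on the assigned arm can affect it. Here the baseline rating is a subjective mark made by an unblinded person, and the schedule places it after the assignment. A participant pleased or disappointed with the assigned arm could rate pain differently at T0. Blinded assessors do not prevent this, because the participant makes the mark.

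The protocol's own Discussion allows that lack of blinding may bias results and that FSN may act partly through psychological effects, so a reaction to assignment is plausible on its own reasoning. An unblinded day-14 rating cannot be avoided in this comparison. An unblinded baseline rating can.

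There is a second, smaller consequence. Anyone who withdraws after allocation but before T0 has been randomised without an observed baseline on the primary measure.

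**Working it through.** **Order of events.** The places that bear on the order are these:

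| Place in the protocol article | What it fixes |
|---|---|
| Outcomes, Table 1 | Allocation at −T1 only; first VAS and WOMAC at T0 |
| Randomization and blinding | Envelope opened at study entry; group follows from the card; participants unblinded |
| Study setting | Assignment described first, baseline assessment after it |
| Interventions | General information gathered before treatment starts, which is not the same as before allocation |
| Inclusion criteria | A pain score above 3 on a 10-point scale is needed for eligibility, so it precedes allocation, but it is not named as the baseline VAS |

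None of these puts the baseline VAS before allocation, and none says that the group is withheld until T0 is complete.

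**How a shift enters the primary comparison.** Let B be baseline VAS and Y be day-14 VAS, so the decrease is D = B − Y. Suppose knowledge of the group moves the between-arm difference in B by b and the between-arm difference in Y by f. Then:

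bias in the contrast of D = b − f

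With f = 0 the baseline shift passes through one for one. If f has the same sign as b, the two partly cancel.

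**Illustration with assumed shifts.** The article gives no value for b or f. The yardstick is the 6.5 mm difference assumed under Sample size calculation. With f = 0:

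- b = 2 mm: 2 / 6.5 = 0.31, or 31%
- b = 4 mm: 4 / 6.5 = 0.62, or 62%

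**Would baseline adjustment remove it?** If baseline VAS were a covariate with slope s, the bias from b alone would be s × b. For an assumed s of 0.3 to 0.7:

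- b = 2 mm: 0.6 to 1.4 mm
- b = 4 mm: 1.2 to 2.8 mm

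Adjustment shrinks the bias but does not remove it, because the covariate itself was measured after allocation.

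**Loss before T0.** Each such participant is 1 of 30, or 3.3% of an arm, with no observed baseline.

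The article states no figure on this point, so there is none to reproduce.

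**The case against.** The strongest reply is that Table 1 may group the enrolment items for convenience and not show sequence. It is coarse elsewhere too: one follow-up column stands for both day 28 and day 42. The interval between −T1 and T0 is not given, and the flowchart in Fig. 1, where the order might be shown, is not available to this review. A reader might infer that participants definitely know their group at T0. The documents do not say that. It is an inference from open assignment and envelope opening at entry, though it is the natural reading and nothing in the text contradicts it.

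Four other stronger readings also go too far:

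- **Loss from the analysis.** A reader might conclude that people lost before T0 fall out of the intention-to-treat analysis. The Statistical analysis section plans multiple imputation, a mixed model for partly missing data and intention-to-treat. They would need an imputed baseline; they are not necessarily excluded. How many there would be is unknown.
- **Percentages as an estimate.** The 31–62% range describes an assumed shift, not this trial, and a same-direction shift at day 14 would reduce the net bias. The unblinded day-14 rating is a separate limitation that the Discussion already acknowledges.
- **All outcomes equally affected.** The self-rating argument applies mainly to VAS and WOMAC. Gait and elastography are instrument measurements, and outcome assessors are blinded.
- **Two incompatible allocation routes.** The text speaks of assignment "for the clinical study at a 1:1 ratio through a central randomization system" and also of details "assembled into random assignment cards that are then sealed in disposable opaque envelopes". The two could work together; the article does not say how. This is a matter of allocation concealment, and the ordering problem does not depend on it.

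The core point survives all of this. The published schedule states an order, that order puts allocation before baseline, and no other text reverses it.

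**Conclusion.** The concern holds in limited form. As written, allocation precedes the baseline assessment, and the self-rated baseline VAS in the primary change score can be marked by participants who probably already know their group. Any differential shift would enter the unadjusted change-score comparison directly, net of any similar shift at day 14.

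The size and direction are unknown. The conclusion rests on three things: that the columns of Table 1 are in time order, that opening the envelope makes the group known to the participant, and that the T0 VAS is the baseline used in the primary outcome. The first two are the plain reading but are not confirmed. If actual practice completes baseline first, the fault is confined to the table, which still needs correcting. A statistical analysis plan could not repair a baseline that was in fact taken after allocation.

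**What to change.** 1. Complete and lock the baseline measures, VAS and WOMAC above all, before the assignment is revealed. State this order under Randomization and blinding.
2. Move allocation in Table 1 to after T0. If practice already follows that order, correct the table only.
3. For each participant already enrolled, record whether baseline was completed before allocation.
4. Separately and secondarily, state how the central randomization system and the envelopes work together. Neither route has to be removed for this fix.

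The cost is a reordering of steps already planned, a table edit, and a record check for those enrolled. The reordering itself adds no assessment.

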#### Primary outcome

KOA is characterized by knee pain as its predominant symptom. Visual Analog Scale (VAS) scores, ranging from 0 to 100 mm, are utilized to objectively quantify pain levels. The primary outcome of this study is the difference in VAS scores between day 14 and baseline measurements. Participants are instructed to indicate the severity of their knee pain by marking a point on a continuous horizontal line segment, with 0 mm representing minimal pain and 100 mm indicating the most severe pain [28].

#### Secondary outcomes

**VAS:** We assess patients’ knee pain using the VAS at baseline, on day 7 and during the follow-up period as secondary outcome indicators.**WOMAC:** The Western Ontario and McMaster Universities Arthritis Index (WOMAC) is widely used to assess the clinical manifestations of knee disorders. We assess the WOMAC scores at baseline, on day 7, day 14, and during the follow-up period. The WOMAC index consists of three sections including evaluation of pain (5 questions), stiffness (2 questions), and physical function (17 questions). A five-level scoring system is applied for each question: asymptomatic (0 point), mild (1 point), moderate (2 points), severe (3 points), and very severe (4 points). Participants complete the index according to their actual conditions. Higher scores indicate more severe symptoms [29]. The temporal evolution of WOMAC scores is analyzed within each group. The scores on each assessment day are also compared between the two groups.**ROM:** Range of Motion (ROM) is evaluated to visually record the motion angle of knee joint. Active ROM, including flexion and extension, is measured at baseline, on day 7 and day 14. For active flexion ROM, the participant are positioned prone with knees at the bed’s edge and lower legs extended naturally. The participant then flexes the knees maximally. Thus, the flexion angle is recorded. For active extension ROM, the participant lies supine with lower limbs extended and ankles slightly elevated by a cushion. The participant then extends the knees maximally. Thus, the extension angle is recorded [30, 31]. Measurements are repeated three times and averaged. Generally, abnormal restriction of active ROM is associated with adhesion of joint cavity, contracture of tendons and muscle weakness. The improvement in active ROM indicates knee healing. Thus, active ROM is evaluated to compare the efficacy of the interventions. (Fig. 4)**Three-dimensional Gait Analysis:** An Opti-Knee 3D motion analysis system equipped with Guangdong Provincial Hospital of Chinese Medicine is used to detect the motion data of the knee joint. The parameters of six degrees of freedom (6 DOFs) are collected and analyzed. The indicator is detected on day 0, day 7 and day 14. The knee joint exhibits complex motion, primarily resulting from the relative movement of the tibia and femur. Based on the principles of the anatomical coordinate system, a three-dimensional femur-tibia coordinate system is established. Thus, it allows the decomposition of the relative motion between the tibia and the femur into 6 DOFs. The DOFs rotating around the coordinate axes includes: internal/external rotation angle, internal/external flip angle, flexion/extension angle. The DOFs translated along the coordinate axes includes: anterior/posterior displacement, superior/inferior displacement, and internal/external displacement [32, 33]. During practice, the participant is asked to undergo approximately 2–3 min of acclimatization. After the bony marks on the body surface are ready for positioning, the participant walks continuously on the exercise board in a natural habitual way at a constant speed of 3.0 km/h. Subsequently, the system collects gait data of 6 DOFs at a frequency of 60 frames/s and an acquisition time of 15 s. The temporal evolution of gait parameters is depicted through curves, and the data are then exported in the form of single-cycle gait data (Fig. 5). In our results, we concentrate on three primary aspects: a comparison of 6 DOFs of the affected knee and those of the healthy side; the evolution of 6 DOFs over the treatment course within the same group; and a comparison of 6 DOFs discrepancies between the two groups. By modeling the participants’ habitual flat walking patterns, we investigate whether the kinematic deficiencies of the affected knee demonstrate an improvement post-treatment, or if the kinematic characteristics of both knees exhibit a tendency to converge.**Shear Wave Elastic Imaging Technology Analysis:** The mean elastic modulus serves as an indicator of muscle tone, which is associated with knee stiffness. We evaluate the Young’s modulus of major muscle groups of knee joint at baseline, on day 7 and day 14. A Supersonic Aixplorer Color Doppler Ultrasound Diagnostic Unit equipped with Guangdong Provincial Hospital of Chinese Medicine is used. Lying flat on the bed, the participant is instructed to relax all body muscles and to straighten both legs naturally. First, 2D ultrasound is used to identify the major muscles. The device is then switched to the SWE mode, with an L15-4 line array probe and a frequency of 4–12 MHz. With the ultrasound set to muscle examination mode, we sequentially measure the vastus intermedius, rectus femoris, vastus lateralis, and tibialis anterior muscles. The probe is lightly placed at the midpoint of the examined muscle belly, and it is parallel to the direction of the muscle fibers. With no pressure applied, skeletal muscles can be regarded as having three layers of depth: the upper layer, the middle layer, and the lower layer. In the ultrasound display, the middle layer is selected to place the sampling box for quantitative analyses. After 5 s, the image is frozen as the shear wave pattern in the box is stable and uniform. The Q-BOX function is launched, with the measurement area set as a 5-mm circle. The system then automatically calculate the mean value of Young’s modulus for the muscle tissues in the Q-BOX (Mean). Each frozen image with the calculation is repeated 3 times, and the mean values of 2 qualified sampling boxes are taken for statistical analyses (Fig. 5). Prior studies have suggested that the higher the value of the elastic modulus of the muscles around the knee, the higher the muscle tone and the tighter the epimysia, which results in restriction to the contraction of muscle fibers and function of the knee joint [34–36]. However, other studies have either failed to find significant results [37] or have reached contrary conclusions [38]. In response to these mixed findings, we investigate the elastic modulus of the major muscles along the force line of the lower extremity, aiming to provide credible evidence.

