Our preliminary study revealed that the modulus of elasticity of the lateral femoral muscle was significantly higher on the affected side than on the healthy side in patients with KOA (*p* < 0.01). It was also found that FSN significantly improved symptoms and signs while reducing the modulus of elasticity of the lower limb skeletal muscles (vastus lateralis, tibialis anterior, and gastrocnemius) of KOA patients (*p* < 0.05), and a related paper is being prepared for publication. Previously, two studies have suggested that FSN therapy applied for the treatment of KOA effectively relieved pain [22, 23]. However, both studies only applied pain-related measures or function-related measures as indicators of efficacy. Few studies have focused on a biomechanical point of view. There are also few published clinical studies that have used objective measures other than scales, such as ultrasonography or imaging. Therefore, the objective of this randomized clinical trial is to investigate the clinical effects and biomechanical mechanisms of FSN for the treatment of elderly patients with knee osteoarthritis. We hypothesized that an intervention programme using FSN for 2 weeks, 3 times per week, would produce better improvements in pain as well as physical function of the knee compared to a positive control group taking celecoxib. Furthermore, this clinical trial also aims to evaluate the ability of FSN to improve gait and lower limb muscle flexibility, which may further help explore the mechanism of FSN therapy.

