### Statistical analysis

All the statistical tests are conducted using a bilateral test, with *P* < 0.05 indicating a statistically significant difference. The Mean ± standard deviation is used for normally distributed measurement data. Non-normal data are presented as the median and interquartile range. Differences in data on outcome measures from baseline to each evaluation time point are analyzed using independent sample t tests or Mann–Whitney U tests, as appropriate, between groups; paired t tests or Wilcoxon tests are used to compare differences in the data for each outcome index at each evaluation time point within the group. In addition, the VAS and WOMAC evaluations are repeated 5 times in this study. Therefore, repeated measures analysis of variance are used for auxiliary analysis. Baseline data (including age, sex, BMI, etc.) are controlled for as confounding factors. Multiple imputation methods are adopted for the analyses of missing data. A generalized linear mixed model is further used for analyses of non-normal and partially missing data, as the interaction effects are also analyzed. The intention-to-treat analyses are performed for the outcomes. SPSS 25 software (IBM SPSS Statistics, New York, USA) is used for the data analyses. Data analyses are conducted by a data analyst who is unaware of allocation and treatment.

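### Read literally, the plan tests WOMAC between groups in two ways (score on the day and change from baseline), with neither named as deciding and neither stated to adjust for baseline WOMAC

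*Protocol article*

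**What the plan says.** The Secondary outcomes section of the protocol article has WOMAC assessed at baseline, day 7, day 14 and during follow-up. It plans a within-group look at change over time and then adds: "The scores on each assessment day are also compared between the two groups". What is compared there is the score on a day.

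The Statistical analysis section sets a between-group method for outcome measures in general, which covers WOMAC: "Differences in data on outcome measures from baseline to each evaluation time point are analyzed using independent sample t tests or Mann–Whitney U tests". What is compared there is the change from baseline. One threshold covers everything: "All the statistical tests are conducted using a bilateral test, with *P* < 0.05 indicating a statistically significant difference".

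The same section notes that "the VAS and WOMAC evaluations are repeated 5 times in this study" and adds a repeated measures ANOVA, labelled auxiliary. It says baseline data are controlled for, giving age, sex and BMI as examples followed by an open-ended 'etc.'. It also plans a generalized linear mixed model for non-normal and partly missing data. Baseline WOMAC is not named as a covariate anywhere.

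Function is part of the trial's hypothesis. The Introduction expects that FSN "would produce better improvements in pain as well as physical function of the knee compared to a positive control group taking celecoxib", and the Conclusion repeats the claim for joint function.

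**The concern.** A comparison of scores on a day and a comparison of changes from baseline are different estimators of the treatment effect. A chance difference between the arms at baseline carries over into the score contrast in one direction and pushes the change contrast in the other. In a trial of 30 per arm such differences are not negligible, so one test can be significant while the other is not.

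If both are run at P<0.05 and neither decides, there are two chances of a positive result for one outcome at one visit. When they disagree, the document does not say which answers the question about function. This is separate from the number of secondary endpoints or visits: it would remain with one endpoint and one visit.

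**Working it through.** **Inputs.** There is no WOMAC figure in the document to reproduce; the sample size of 60 rests on the VAS and is taken as given.
- Per arm: 30 under intention to treat with imputation, or 30 × 0.9 = 27 after the stated 10% dropout.
- Test level: two-sided 0.05 (Statistical analysis).
- Correlation ρ between baseline and follow-up WOMAC: not given; assumed 0.3, 0.5 and 0.7.
- Also assumed: normal scores, equal variance at baseline and follow-up, t tests, effects in units of the score SD.

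**Step 1: how closely the two tests are linked.** Let D0 and D1 be the between-arm differences at baseline and follow-up. With SD 1 and n per arm:
- Var(D1) = 2/n
- Var(D1 − D0) = (2/n) × 2(1 − ρ)
- Cov(D1, D1 − D0) = (2/n)(1 − ρ)

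The correlation of the two test statistics is therefore (1 − ρ)/√(2(1 − ρ)) = √((1 − ρ)/2), which is 0.59, 0.50 and 0.39 at ρ = 0.3, 0.5 and 0.7. The tests are far from interchangeable.

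**Step 2: false positives at one visit.** The chance that at least one of two such statistics exceeds 1.96 in absolute value, from the bivariate normal, is 8.8%, 9.1% and 9.4%. Simulation with t tests at 27 and 30 per arm gives 8.6% to 9.5%. Two independent tests would give 1 − 0.95² = 9.75%, so the second contrast adds nearly as much error as an unrelated one.

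**Step 3: how often the verdicts differ at one visit** (simulated, 27 per arm, then 30 per arm).

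| True effect | ρ = 0.3 | ρ = 0.5 | ρ = 0.7 |
|---|---|---|---|
| 0 | 8%, 7% | 8%, 8% | 9%, 9% |
| 0.25 SD | 17%, 17% | 18%, 20% | 24%, 26% |
| 0.5 SD | 30%, 31% | 33%, 34% | 41%, 40% |
| 0.77 SD | 27%, 25% | 23%, 20% | 21%, 17% |
| 1.0 SD | 13%, 10% | 8%, 5% | 5%, 3% |

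Among the effects tried, disagreement is largest at 0.5 SD and falls away on both sides.

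**Step 4: power of one baseline-adjusted contrast.** The noncentrality is 0.5/(s × √(2/27)) = 1.837/s, where s is 1 for the score, √(2(1 − ρ)) for the change, and √(1 − ρ²) for the score adjusted for baseline.

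| Power at 0.5 SD, 27 per arm | ρ = 0.3 | ρ = 0.5 | ρ = 0.7 |
|---|---|---|---|
| Score | 44% | 44% | 44% |
| Change | 33% | 44% | 64% |
| Adjusted for baseline | 47% | 55% | 71% |

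The adjusted analysis has the most power at each ρ. It also removes the choice. If Y = a + τ·arm + b·baseline, then Y − baseline = a + τ·arm + (b − 1)·baseline, so τ is the same whether score or change is the response.

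**The case against.** The strongest reply is that there is only one contrast. The WOMAC sentence sits in an outcome description, names no test and no P value, and may simply say in plain words what the Statistical analysis section then specifies as change from baseline. The Introduction speaks of improvements, and the primary outcome is itself a day 14 minus baseline difference. This reading is possible, so the conflict is the literal reading of the sentence and not the only one. It does not dispose of the point: scores on a day are not changes, and if change was meant, correcting the sentence is part of the same repair.

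A second reply is that the plan already has some ranking and adjustment: an auxiliary ANOVA, control for baseline data, and a mixed model. That is right, and it limits the point. But the auxiliary label does not rank the two between-group contrasts, baseline WOMAC is not among the named covariates, and a t or Mann–Whitney test takes no covariate.

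Third, an article may leave the decisive visit for a secondary outcome, or the choice of total or function subscale, to an analysis plan that is not shown. That stands, and those omissions are not counted here.

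A reader might also infer several stronger claims that the document does not support:
- **A significance test between arms at baseline.** No such test is stated; it follows only if baseline counts as an assessment day.
- **A false-positive rate of 26% to 28% over the four post-baseline visits.** That is what simulation gives for both contrasts together, but change scores alone already give about 15% to 16%. Most of the figure is visit multiplicity.
- **That the function hypothesis stands or falls on WOMAC.** Active range of motion and gait are also planned, and range of motion is expressly used to compare efficacy.

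**Conclusion.** The point holds as an inconsistency between two sections of the article. Read literally, they set two unadjusted between-group contrasts for WOMAC at the same visit and level, with neither deciding. If both are used, the false-positive chance at one visit is about 9% instead of 5%. Disagreement on significance runs from about 8% with no effect, through 30% to 40% at 0.5 SD, to 3% to 13% at 1.0 SD.

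It would be too strong to say that the function hypothesis can be called either way on any data set. Disagreement is a material risk at moderate effects and small at large ones, and 30% to 40% is near its peak. These figures rest on the assumed correlation of 0.3 to 0.7, normal scores with equal variances, and 27 to 30 analysed per arm. WOMAC is secondary, so the VAS primary conclusion is untouched. The repair is worth making because it is cheap and improves the analysis.

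**What to change.** Reconcile the WOMAC paragraph in Secondary outcomes with the Statistical analysis section by stating one between-group contrast: the post-baseline WOMAC score compared between arms with baseline WOMAC as a covariate. Fit it by ANCOVA, or by the mixed model already planned with that covariate added. Keep WOMAC scores by day as descriptive summaries without P values.

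The cost is a few sentences in two sections. Baseline WOMAC is already collected, so no extra data, visits or patients are needed. The small downside is that the investigators give up the second set of P values.
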